### Process Measures

5.3

Testing intensity is analyzed, not solely as a fidelity check but as a prespecified outcome. For each targeted category—ABG samples, venous laboratory tests, and chest radiographs—counts per patient‐day are analyzed in a mixed‐effects negative binomial model with a log link, an offset for observed patient‐days, a random intercept for cluster, and fixed effects for calendar period and treatment condition, specified analogously to the primary analysis. Effects are reported as incidence rate ratios with 95% CIs, separately by category and pooled across the three. Because these counts are ascertained from 5‐day monitoring windows at baseline and at 1 and 3 months after transition rather than continuously, the estimates describe testing intensity during sampled windows and are reported as such. Importantly, where high‐resolution electronic health record data are available, a supporting analysis using continuous data across the full study period is reported for those clusters and its agreement with the sampled estimates described. Departmental orders for vacutainer tubes and blood‐gas syringes are reported at cluster‐period level as a third, independent indicator of testing volume.

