### Primary Analysis—Mortality (Non‐Inferiority)

5.2

The primary analysis fits a generalized linear mixed‐effects model for 30‐day mortality with a binomial distribution and logit link. The model includes a fixed effect for treatment condition (intervention versus control), fixed effects for calendar time modeled as categorical monthly periods, fixed‐effect adjustment for the prespecified baseline covariates (SAPS 3 score, age, sex, admission type [emergency vs. planned], and ICU category [SIR Levels 1–3]), and a random intercept for cluster, implying an exchangeable within‐cluster correlation structure. Sensitivity analyses will explore alternative correlation structures, including a random cluster‐by‐period effect allowing the within‐period correlation to exceed the between‐period correlation. Because a minority of patients contribute more than one care episode, the model also includes a random intercept for patient nested within cluster. A sensitivity analysis restricted to each patient's first ICU admission during the study period will be reported.

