#### Stepped‐Wedge Design Considerations

5.4.1

Random effects for clusters to account for unmeasured cluster‐level confounders.Sensitivity analyses using different correlation structures.

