##### Outcomes

5.11.1.5

30‐day mortalityICU length of stayUnplanned ICU readmission within 72 h from dischargeMortality data with precise timing.

*Process measures—Local monitoring*: Clinical monitors will study the utilization/frequency of ABGes, venous laboratory testing, and chest radiography during both control and intervention phases. Since this data is not registered in SIR, an electronic Case Report Form (eCRF) will be created to capture:
Number of ABG samples per patient‐dayNumber of venous laboratory tests per patient‐dayNumber of chest x‐rays per patient‐dayProtocol adherence measures

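### The main testing-intensity model has no cluster-by-window effect, so its rate-ratio intervals can be too narrow unless the data are analysed as one row per cluster-window

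*Protocol article*

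**What the plan says.** Section 5.3 (Process Measures) fits a log-link negative binomial mixed model to the counts of each test category. The random and fixed effects it names are "a random intercept for cluster, and fixed effects for calendar period and treatment condition". Exposure time enters through "an offset for observed patient‐days". The same sentence ends by calling the model "specified analogously to the primary analysis". Rate ratios with 95% intervals are to be reported by category and pooled over the three. The section states that "these counts are ascertained from 5‐day monitoring windows at baseline and at 1 and 3 months after transition", so a cluster has one control window and two intervention windows.

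Two features of the mortality model in Section 5.2 matter here. First, because some patients have several care episodes, "the model also includes a random intercept for patient nested within cluster". Second, alternative correlation structures are left to sensitivity analyses, "including a random cluster‐by‐period effect allowing the within‐period correlation to exceed the between‐period correlation". Section 5.4.1 adds, without naming an outcome, "Sensitivity analyses using different correlation structures".

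Section 5.11.1.5 says that "an electronic Case Report Form (eCRF) will be created to capture" numbers of tests per patient-day. Nowhere is it stated whether a row of the analysis file is a patient-day, a patient or a cluster-window.

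**The concern.** All patients in one 5-day window share that week's case mix, staffing and ordering habits. The before-after contrast within a unit compares a few such weeks, so variation between weeks has to enter the standard error. A cluster intercept does not carry it, because it is constant across a unit's windows. The calendar-period effects do not carry it either, because they are common to all units. A patient intercept, if intended, handles repeated days of one patient but not what different patients in the same week have in common.

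What is at stake is the precision of a prespecified outcome. Section 4.2 lets testing intensity count as evidence of benefit once non-inferiority for mortality is shown. Section 5.1 gives such outcomes no formal non-inferiority test, so the estimate and its 95% interval are the whole inference. The pooled ratio has a related gap: it combines three counts from the same patients and days, and Section 5.3 does not say how.

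**Working it through.** **The plan's own figure.** There is none to reproduce. The article gives no variance, intraclass correlation, precision or power for the rate ratios. Its 89% power refers to mortality and does not bear on this point.

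**Inputs from the article.** 36 clusters (Section 2.5), so 36 × 3 = 108 cluster-windows; windows of 5 days; negative binomial model with cluster and period effects (Section 5.3).

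**Inputs assumed, because the article gives none.** About n = 8 patients per window with about d = 3 days each; patient SD 0.4 and window SD 0, 0.1 or 0.2 on the log scale; negative binomial size k = 5; mean μ of 8 blood gases or 0.5 radiographs per patient-day; true rate ratio 0.90.

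**Hand check.** The log rate of one window has approximate variance

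T = σ_w² + σ_p²/n + e/(nd), with e = 1/μ + 1/k.

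Without a window or patient term, all variation goes into the dispersion and is averaged over rows as if they were independent:

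- patient-day rows: D = (σ_w² + σ_p² + e)/(nd)
- patient rows: P = (σ_w² + σ_p² + e/d)/n

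For blood gases e = 1/8 + 1/5 = 0.325 and σ_p² = 0.16. With σ_w = 0.2:

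- T = 0.04 + 0.16/8 + 0.325/24 = 0.0735
- D = (0.04 + 0.16 + 0.325)/24 = 0.0219, so true SE / model SE = √(0.0735/0.0219) = 1.83
- P = (0.04 + 0.16 + 0.108)/8 = 0.0385, so the ratio is √(0.0735/0.0385) = 1.38

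Coverage is about 2Φ(1.96/ratio) − 1, which gives 72% and 84%. With σ_w = 0, T = 0.0335. The ratio is then 1.29 for patient-day rows (87% coverage) and 1.00 for patient rows (95%).

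**Simulation.** 600 data sets per scenario, with cluster intercepts fitted as fixed effects to approximate the random intercept, and no patient or window term. Entries are true SE / model SE, then coverage of the nominal 95% interval.

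| Counts, window SD | Patient-day rows | Patient rows | Cluster-window rows |
|---|---|---|---|
| Blood gas, 0 | 1.29, 87% | 0.97, 96% | 0.95, 96% |
| Blood gas, 0.1 | 1.52, 80% | 1.13, 92% | 1.01, 95% |
| Blood gas, 0.2 | 1.81, 73% | 1.33, 86% | 0.99, 95% |
| Radiograph, 0.1 | 1.18, 91% | 1.08, 93% | 1.04, 94% |
| Radiograph, 0.2 | 1.27, 89% | 1.16, 92% | 1.02, 95% |

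The Monte Carlo standard error of coverage is √(0.80 × 0.20/600) = 1.6 points near 80% and 0.9 points near 95%. The simulation agrees closely with the hand formula. Patient rows remove the repeated-days problem but not the window problem. With cluster-window rows the window variation falls into the dispersion parameter, and the stated model covers as it should.

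**What this does to a reported interval.** Blood gases, window SD 0.2, estimate 0.90:

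- Patient-day rows: the model SE of 0.051 gives 0.90 × exp(±1.96 × 0.051) = 0.81 to 0.99; the true SE of 0.093 gives 0.75 to 1.08.
- Patient rows: the model SE of 0.069 gives 0.79 to 1.03; the true SE of 0.092 gives 0.75 to 1.08.

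**The case against.** The strongest reply is that the defect depends on how the wording is implemented. A reader might infer from the listed terms that the model has a cluster intercept and nothing else, and so treats days of the same patient as independent. The text does not establish that: the analogy clause can fairly be read as carrying over the patient intercept. The offset also points away from patient-day rows, where it would be log(1) = 0 throughout. With cluster-window rows, which the wording allows, there is no coverage problem. These points stand, and they make the worst column of the table the least likely layout. They do not rescue patient rows, because the primary model that serves as the analogue has no cluster-by-period effect in its main form either.

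Section 5.4.1 promises other correlation structures, but as sensitivity analyses, which leave the headline interval as it is. Section 5.3 limits the estimates to the sampled windows and adds electronic-record data and consumables orders. These help credibility but do not correct the interval. How the categories are pooled is not stated; if the counts are simply summed, that part of the concern falls away.

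It can also be said that an article leaves such detail to a fuller plan. But Section 2.5 presents this publication as both protocol and analysis plan, and Section 5.3 does list the model's terms. The point concerns what is listed.

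**Conclusion.** The point holds in conditional form. The main process model has no cluster-by-window effect under either reading of Section 5.3. If rows are patient-days or patients and testing varies from week to week within a unit, the rate-ratio intervals are too narrow. Under the assumed SDs the loss of coverage is moderate to marked for frequent tests and small for radiographs. With cluster-window rows it is absent. The size rests on SDs, patient numbers and test rates that the article does not give.

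Three stronger conclusions might be inferred and are not supported:

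- That the intervals are too narrow in every case. This depends on the row level and on the window variation, neither of which is stated.
- That having few windows narrows the intervals. Few windows reduce precision; it is the omitted variance component that misstates it.
- That the trial's main decision is at risk. The 5% fidelity criterion in Section 4.3.1 is worded on the observed reduction with no confidence bound, and the mortality analysis is a separate model. Section 5.1 makes the process outcomes supportive only.

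**What to change.** State the row level in Section 5.3 and say whether the patient intercept applies. Then do one of the following in the main process model:

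- Add a random cluster-by-window intercept, together with a patient intercept if rows are patient-days.
- Analyse one row per cluster-window and category, with small-sample cluster-robust intervals.

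For the pooled ratio, either sum the three categories or treat category as a repeated measure within the cluster-window, and say which. The change is to analysis-plan wording only and needs no new data. Section 2.5 says that no outcome data had been extracted or examined when the versions were finalized. The price is slightly wider intervals.

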### Handling of Clustering and Temporal Effects

5.4

#### Stepped‐Wedge Design Considerations

5.4.1

Random effects for clusters to account for unmeasured cluster‐level confounders.Sensitivity analyses using different correlation structures.

#### Handling of Missing Data

5.4.2

Complete case analysis as primary approach given high data completeness in the SIR (> 95%).Multiple imputation using chained equations if missing data > 10% for key variables.Missing data patterns will be assessed and reported.Sensitivity analyses comparing complete case and imputed results.

### Sensitivity Analyses

5.5

*Time trend specifications*: Alternative modeling of temporal trends.
*Outlier ICUs*: To assess the influence of potentially outlying clusters, a binary indicator variable identifying these clusters will be included in the model both as a main effect and in interaction with treatment.
*Baseline period*: Varying length of baseline observation period.
*Minimal detectable difference*: Minimal detectable difference will be calculated to evaluate the assumptions of power analysis.To assess for the gradual onset of the treatment effect following each cluster's transition from control to intervention, the treatment variable will be replaced by a categorical variable with the following levels: “Before switch,” “0–7 days after switch,” “8–14 days after switch,” and “> 14 days after switch.”If ICU drop‐out or wrongful randomizations occur, a per‐protocol analysis will be performed to account for this.Contemporaneous external comparison: Because SIR captures over 95% of Swedish ICU admissions, admissions to nonparticipating Swedish ICUs over the same calendar months provide a contemporaneous, non‐randomized external comparison. Risk‐adjusted 30‐day mortality is compared between participating and nonparticipating units by calendar period, adjusted for SAPS 3, age, sex, admission type, and ICU category, to characterize secular trend and background fluctuation in mortality unrelated to the intervention and to provide an indirect check for diffusion of CW practice beyond the trial. Because participation was not randomly assigned and participating units differ from nonparticipating units in size, category, and case mix, this comparison is descriptive and is not interpreted as an effect estimate.

### Subgroup Analyses

5.6

Prespecified subgroup analyses will examine intervention effects across:
ICU Category 1, 2, and 3 according to the SIR definitions.

### Blinding

5.7

Because the intervention changes clinical routines at the unit level, ICU personnel, treating physicians, and local investigators cannot be blinded to allocation status, and no attempt at blinding of clinical staff is made. Patients are not actively informed of their unit's phase but are not formally blinded. No blinding of registry personnel is claimed; however, the primary outcome—30‐day all‐cause mortality—is ascertained automatically through SIR's linkage to the Swedish population register, and the secondary outcomes are extracted from routinely registered SIR data whose collection is identical in control and intervention periods and independent of the trial. Outcome ascertainment is therefore objective and not susceptible to assessor bias, which is the principal protection against detection bias in this open‐label design.

Data management and statistical analysis will be performed with the treatment condition held as a coded exposure variable until the analysis code is finalized, so that the analyst is blinded to allocation during code development; the statistical analysis code will be finalized and archived before the exposure coding is revealed. Because the trial is open‐label at the cluster level, there is no individual participant allocation that could be revealed, and no unblinding procedure is required. Follow‐up for the primary outcome is complete by construction: 30‐day mortality is ascertained through SIR's linkage to the Swedish population register rather than through participant contact, so loss to follow‐up is not a meaningful mechanism in this trial.

### Safety Monitoring

5.8

A formal data monitoring committee with interim efficacy analyses is not established, which we consider justified by the pragmatic registry‐based design, the minimal‐risk nature of an intervention that removes only non‐indicated routine testing while preserving all clinically indicated diagnostics, and the absence of any planned early stopping for benefit. Safety oversight is instead provided by an independent safety review group comprising [name] and [name], both senior intensivists with deep knowledge of SIR data, none of whom are trial investigators.

The group reviews unblinded monthly reports generated from SIR, comprising 30‐day mortality and the secondary safety outcomes by cluster and by intervention status, until the last patient has completed follow‐up. The group may recommend continuation, modification, suspension of the intervention at individual ICUs, or termination of the trial; recommendations are made to the principal investigator and steering committee, who are responsible for acting on them and for informing participating ICUs and, where required, the Swedish Ethical Review Authority. If interim monitoring indicates increasing mortality or adverse changes in any secondary safety outcome, the affected ICU will be contacted to discuss appropriate action. A quantitative trigger is prespecified. Review by the safety review group is initiated whenever a cluster's observed 30‐day mortality during its intervention periods exceeds the upper bound of the 95% prediction interval derived from that cluster's own historical SIR mortality for the corresponding calendar months, or whenever the pooled intervention‐versus‐control mortality difference on the cumulative monthly report exceeds 3 percentage points. Meeting a trigger prompts review and, at the group's discretion, contact with the affected unit and a recommendation to the steering committee; it does not automatically suspend the trial.

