#### Non‐Inferiority Power Analysis

4.4.1

We conducted a non‐inferiority‐based power calculation for our primary outcome of mortality, using a non‐inferiority margin of 3%. The analysis is based on data from the SIR.

The choice of a 3‐percentage‐point margin was made on the following grounds. First, the intervention removes routine, non‐indicated testing while explicitly preserving all clinically indicated diagnostics, and the aggregate randomized and observational evidence on diagnostic‐test reduction in intensive care shows no signal of increased mortality [22]; a true effect approaching the margin is therefore considered implausible a priori. Second, mortality is deliberately complemented by more sensitive safety outcomes that would be expected to deteriorate before any mortality effect became detectable, together with monthly safety monitoring throughout the trial. Third, the margin must be weighed against feasibility: demonstrating non‐inferiority within a substantially narrower margin (e.g., 1–2 percentage points) would require a trial several times larger, running over multiple years, which is not achievable while ICUs are already adopting CW practice outside trial conditions; the present design represents the strongest randomized evidence obtainable before uncontrolled implementation makes a controlled evaluation impossible. On balance, the steering committee judged that, for an intervention with documented benefits in reduced iatrogenic anemia, reduced resource use and reduced environmental impact, a 3‐percentage‐point margin represents the largest mortality difference that could be considered clinically acceptable, while the a priori expected difference is null. The margin may also be set against those adopted in recent critical care non‐inferiority trials with all‐cause mortality as the primary outcome. EVERDAC, comparing early with deferred arterial catheterization in shock, used a margin of 5 percentage points against a control‐group 28‐day mortality of 36.9% [34]. BALANCE, comparing 7 with 14 days of antibiotic therapy for bloodstream infection, used 4 percentage points against a control‐group 90‐day mortality of 16.1% [35]; three earlier trials in that field used 10 percentage points. In absolute terms, the present margin is smaller than both. In relative terms, 3 percentage points against a baseline 30‐day mortality of 18% corresponds to a risk ratio of 1.17, which lies between the corresponding figures for EVERDAC and BALANCE. The choice of margin does not by itself determine what would justify a change in practice; that question is addressed in the Discussion. Expressed in absolute terms, a true effect lying exactly at the margin would correspond to approximately 670 additional deaths across the projected 22,428 care episodes. The trial is therefore designed to exclude, rather than to detect, harm of this magnitude, and the secondary safety outcomes together with monthly monitoring are intended to identify smaller signals earlier.

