
#### Power Calculation

4.4.2

Sample size was calculated using the swCRTdesign package in RStudio.

Parameters:

*Stepped wedge design*: As shown in Figure 1.
*Primary endpoint*: 30‐day mortality.
*Design*: Non‐inferiority trial.
*Number of patients per cluster and time period*: A total of 38 ICUs were included in the analysis. Two ICUs were merged into a single cluster because they share staff, resulting in *37 distinct clusters*. The stepped‐wedge design comprised *13 time periods*. Based on historical data, the total number of ICU admissions during the 13‐month study period was estimated to be *22,625 episodes*, derived from Swedish Intensive Care Registry admission data for the participating clusters over the corresponding calendar period [29]. Under these assumptions, the average number of ICU admissions per cluster and time period was calculated as 22,625 ÷ 13 ÷ 37 ≈ *47 admissions*.These are the parameters prespecified before recruitment opened. Following the withdrawal of one cluster, the corresponding figures are 22,428 episodes across 36 clusters and 13 periods, approximately 47 admissions per cluster‐period, a reduction of 0.9% that does not materially affect the power calculation, which has therefore not been repeated.
*Alpha level*: 0.025 (one‐sided 97.5% CI).
*Intraclass correlation coefficient (ICC)*: 0.009
○The ICC was calculated using historic data via a generalized linear mixed model. To account for differences in baseline mortality across ICU types, the model included:
A variable distinguishing ICU category [1, 2, 3].A variable indicating whether the ICU was a thoracic unit, which has distinct expected mortality rates.

*Treatment effect was assumed to be homogeneous across clusters*.
*No fixed time trends were assumed*.

*Non‐inferiority margin assumption for 30‐day mortality*: Based on historical data, the mean baseline 30‐day mortality across the relevant clusters was estimated at 18%, based on Swedish Intensive Care Registry historical data for the participating clusters [29]. The non‐inferiority margin was defined as an absolute risk difference of 3 percentage points. Assuming the same baseline mortality, this corresponds to a relative risk of 1.17 and an odds ratio of approximately 1.21.

*Power to demonstrate non‐inferiority under the assumptions stated above*: 89%. A Power > 80% will be considered acceptable to demonstrate non‐inferiority.

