## Discussion

7

The WICH‐ICU trial will address several important knowledge gaps in critical care and implementation science.

The WICH‐ICU trial will provide randomized evidence on the safety of systematically implementing CW recommendations in intensive care, an area where high‐quality evidence is currently scarce [22, 24]. By pairing 30‐day mortality with a set of more sensitive safety outcomes, and by embedding the intervention in routine care across a national registry, the trial is designed to detect any safety signal while remaining pragmatic and generalizable.

The design has several strengths. The stepped‐wedge approach maximizes statistical efficiency while ensuring that every site eventually receives the intervention; the registry‐based approach leverages a high‐quality, near‐complete national data infrastructure; cluster randomization minimizes contamination and reflects real‐world implementation; and the multi‐site design, covering roughly half of Swedish adult ICU admissions, enhances generalizability. The interventions are grounded in established professional recommendations, are designed for routine clinical use, and are supported by a local‐champion model that promotes sustainability.

The non‐inferiority margin defines the decision rule for a prespecified statistical hypothesis; it is not the threshold at which we would recommend a change in practice. Because the intervention removes routine testing rather than adding treatment, and because the benefits at stake are efficiency and environmental rather than clinical, the trade‐off is asymmetric: a mortality difference lying well within the margin could still be judged unacceptable for an intervention of this kind. We will therefore report the point estimate and the full confidence interval for the adjusted risk difference alongside the formal non‐inferiority conclusion, and we state in advance that a point estimate indicating excess mortality under the intervention would not, in our view, support de‐implementation of the targeted diagnostics even were the upper confidence bound to fall below 3 percentage points. As noted above, a true effect at the margin would correspond to approximately 670 additional deaths across the projected care episodes; a difference half that size would remain clinically material and will be reported as such.

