Several limitations warrant consideration. Secular trends may confound intervention effects, although calendar time is modeled explicitly; registry data may not capture all relevant confounders; local implementation may vary between sites; and knowledge of the intervention could influence practice during control periods. As a single‐country study, the results may not fully generalize to healthcare systems with different practice patterns, culture, or resources.

Beyond patient safety and resource use, the trial will quantify the environmental impact of reducing low‐value testing, contributing to an emerging evidence base that links CW to healthcare sustainability [26, 40]. The trial does not undertake a formal health‐economic evaluation, and we make no claim about monetary savings. Most of the short‐run cost of a blood gas, a laboratory panel or a chest radiograph is staff time and installed capacity, both fixed over the horizon of this trial; reduced test volume does not become reduced expenditure unless that capacity is redeployed, and internal cross‐charging between clinical and service departments can offset an apparent saving within the same system. Reductions in testing are therefore reported in natural units and should not be read as realized savings. The environmental outcome is less exposed to this argument, since avoided consumables, reagents, and their transport are variable inputs whose emissions are avoided directly, and it is for this reason that CO_2_e rather than cost is reported as the efficiency‐side outcome. If non‐inferiority is demonstrated, the results will support evidence‐based de‐implementation of low‐value ICU diagnostics, and the design may serve as a model for similar evaluations in other settings and clinical areas.

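### The trial-wide mortality trigger equals the non-inferiority margin and states no calendar adjustment, so it responds poorly to half-margin harm and a calendar trend can shift it

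*Protocol article*

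**What the plan says.** Section 5.8 (Safety Monitoring) replaces a formal data monitoring committee with an independent safety review group that reads unblinded monthly reports by cluster and by intervention status. It sets two quantitative triggers for review. One compares each cluster with its own history for the same calendar months. The other is trial-wide and is met when the pooled "mortality difference on the cumulative monthly report exceeds 3 percentage points". No adjustment or measure of uncertainty is given for the second.

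Section 4.4.2 states: "The non‐inferiority margin was defined as an absolute risk difference of 3 percentage points". Section 4.4.1 puts harm at that margin at "approximately 670 additional deaths across the projected 22,428 care episodes" and adds that the secondary safety "outcomes together with monthly monitoring are intended to identify smaller signals earlier". The Discussion returns to the margin and says that "a difference half that size would remain clinically material and will be reported as such".

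On calendar time, the Discussion concedes: "Secular trends may confound intervention effects". The remedy that it names is explicit modelling. The primary model in section 5.2 has categorical months, SAPS 3 and other covariates. Section 5.8 mentions nothing comparable for the pooled trigger.

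**The concern.** There are two separate problems.

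**Calendar time.** In a stepped wedge, control time comes early and intervention time comes late. A crude cumulative difference by intervention status therefore carries any season or secular trend along with the effect. The primary analysis deals with this, and the trigger, as described, does not. A falling or winter-peaking trend can hide harm, and a rising one can suggest harm that is not there.

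**Level.** A rule that compares a point estimate with 3 points is met about half the time when the true excess is 3 points. For a smaller excess it is met less and less often as data accrue. That fits poorly with a plan that relies partly on monthly monitoring to pick up smaller signals, and that regards half the margin as material.

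With no formal data monitoring committee, this is the only quantitative rule that looks at the trial as a whole.

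**Working it through.** **The plan's own figures.** Deaths at the margin: 0.03 × 22,428 = 673, the stated 670. Half the margin: 0.015 × 22,428 = 336. Stated power is 89%. With a stepped-wedge model (random cluster intercept, categorical periods, 37 clusters, 13 periods, 47 per cell, ICC 0.009) and the binomial variance at 21%, the SE is 0.934 points. Power is Φ(3/0.934 − 1.96) = Φ(1.25) = 89.5%. Taking the variance at 18% or at the midpoint gives 91–93%. The power figure is not in dispute.

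**Inputs for the trigger.** Baseline 18%, ICC 0.009, 36 clusters, 13 periods and 10 sequences are from sections 3.1 and 4.4.2. Assumptions: 48 episodes per cell (22,428/468 = 47.9), equal cluster sizes, first switch in month 2 (month 3 also tried), a crude difference, no reporting lag, and trends whose size the article does not give. The method is simulation of the cumulative intervention-minus-control difference at each monthly report.

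**Time gap.** With four clusters in each of the first six sequences and three in the rest, intervention cluster-months are 4 × (12+11+10+9+8+7) + 3 × (6+5+4+3) = 282 of 468. Their mean month is 9.08, against 3.85 for control, a gap of 5.23 months.

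**Calendar bias of a crude difference.**
- Linear fall of 2 points over 12 steps: −(2/12) × 5.23 = −0.87 points. A fall of 1 point gives −0.44.
- Winter-peaking season of 1-point amplitude: −0.67 points.
- Rise of 2 points: about +0.87.

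**No trend, true excess 1.5 points.** The probability of firing at one report is about Φ(−1.5/SD).

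| Report | SD (points) | Fires |
|---|---|---|
| First | 3.4 | 32% |
| Month 6 | 1.24 (1.4 if first switch in month 3) | 12% (14%) |
| Month 10 | 0.9 | 5% |
| Month 13 | 0.75 | 2% |

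About 46% fire at some report, but only 15% at any report from month 6 on (first switch in month 2). With no effect, 19% fire at the first report and about 22% at some report.

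**True excess 3 points, last report.** No trend: 50%. Fall of 2 points: Φ(−0.87/0.75) = Φ(−1.16) = 12%. Winter season: Φ(−0.67/0.75) = Φ(−0.89) = 19%, and 19–20% when simulated.

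**Per-cluster trigger** (47 episodes a month, 18% baseline). The upper bound is about 29–31% after 1 month and 21–22% after 12. At a true 1.5-point excess, a given cluster fires with probability 5%, rising to 13–16%, against 2.5% by chance. Over 36 clusters, the chance of at least one false alarm at one look is 1 − 0.975^36 = 60%.

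**After adjustment for cluster and period, cut-off kept at 3 points.** The SE is 1.20, 0.93 and 0.88 points at months 6, 10 and 13. At a true 1.5-point excess the trigger fires in Φ(−1.5/1.20) = 11%, Φ(−1.5/0.93) = 5% and Φ(−1.5/0.88) = 4%. Adjustment removes the calendar bias but not the insensitivity.

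**The case against.** Much can be said for the plan, and several parts of it stand.

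- Section 4.4.1 gives the task of finding smaller signals to the secondary outcomes together with monthly monitoring, not to this trigger. A pooled trigger at the margin is therefore not a contradiction on its face.
- The group sees every monthly report whether or not a trigger is met. Section 5.8 has the unit contacted on adverse change in any secondary safety outcome, and section 5.9 sends any safety signal and suspected related serious harms to review. These routes are real, but they have no numerical criterion.
- The per-cluster trigger is matched to calendar month and so meets the seasonal point for single units. It has little power for a small effect spread over all of them.
- The rule is checked monthly. Over all reports in the same simulation, a true 3-point excess fires at least once in about 81% of trials without a trend and 74% with the 2-point fall. The drop from 50% to 12% describes the last report, not the whole trial.
- A rising trend works the other way, though a 2-point rise lifts firing with no effect only from about 22% to 24%.
- The article does not say that the difference is crude, and the full protocol is deposited elsewhere. The adjustment may be specified there.

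A reader might also infer bias from unit mix, since thoracic status is a feature "which has distinct expected mortality rates". Allocation was randomized and stratified by ICU category and size, so unit mix adds noise rather than a systematic shift. The simulated SD includes cluster variation at the stated ICC. Because that ICC was estimated net of category and thoracic status, the crude SD could be somewhat larger.

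**Conclusion.** The point holds in a limited form. The pooled trigger equals the margin and carries no stated calendar adjustment, although the article names secular trend as a confounder and models it in the primary analysis. If the difference is crude, a 2-point fall biases it by about −0.9 points and a 1-point winter season by about −0.7. A true 3-point excess would then fire the last report in about 12% or 20% of trials instead of 50%. These trend sizes are assumptions. Without any trend, the half-margin excess fires in 12–14% of trials at month 6 and 2% at month 13.

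Three stronger readings are not supported. The trigger is not incapable of responding to smaller harm: 46% of trials fire at some report against 22% under no effect, although mostly from early noise. It is not the only safeguard, nor the one to which the article entrusts smaller signals. Masking is not certain, because it depends on the direction of the trend and on the comparison being crude. Leaving out clustering would also overstate the case: a plain binomial SE of about 0.53 points puts firing at 0.2% for a 1.5-point excess at the last report, against about 2% with clustering.

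**What to change.** Compute the pooled difference on each cumulative report from the primary model, or at least with cluster and calendar-period effects, and show it with its confidence interval. State this in section 5.8.

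Separately, ask the safety review group to reconcile the trigger level with section 4.4.1 and the Discussion, and to record the reasoning. Adjustment alone will not do this, since at 3 points it still fires in only 4–11% of trials at a true 1.5-point excess. The level is the group's judgement between sensitivity and false alarms, and none is proposed here.

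The cost is a scripted model fit each month, a slightly larger SE late in the trial (about 0.88 against 0.75 points at month 13) and possibly more reviews. Meeting a trigger prompts review only and does not automatically suspend the trial.
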